## Abstract

**Introduction:**

Timed and targeted care for families (ttCF) is a community-based intervention implemented under the Maternal, Newborn, and Child Health (MNCH) project (2021–2025) in Eastern Visayas, Philippines. The ttCF aims to improve maternal and child health during the first 1,000 days of life. The study presents the design of impact and implementation process evaluations of the ttCF program.

**Methods:**

A comprehensive evaluation framework was developed, including (1) a quasi-experimental study with 6 intervention and 6 comparison municipalities, (2) multiple cross-sectional surveys only in 16 intervention municipalities, and (3) a process evaluation guided by the RE-AIM framework (reach, impact/outcomes, adoption, implementation and maintenance). In intervention areas, barangay health workers (BHWs) conducted 12 structured home visits from pregnancy through the child’s second birthday. Comparison areas received standard government health services. The outcomes include continued health and nutrition during the first 1,000 days of life, and the utilization of antenatal and postnatal health services. Data sources include household surveys, monitoring records, and qualitative data collection.

**Results:**

In the quasi-experimental study, 1,518 pregnant or mothers with children under 2 years were enrolled, with 1,313 followed up 1 year later. For the cross-sectional surveys, 720 women were assessed at baseline and 896 at midline. As of December 2024, over 6,280 women were registered in the monitoring database. A total of 61 participants, including mothers, husbands, family members, and BHWs, were assessed at focus group discussions and in-depth interviews.

**Discussion:**

The comprehensive evaluation will provide an in-depth understanding of the ttCF impact pathway, strategic monitoring, and the quality of program implementation. The evidence will inform the strengthening of community health system by promoting BHW engagement and guiding community interventions to improve maternal and child health outcomes in the Philippines.

## Introduction

1

Between 1990 and 2023, a remarkable decline in child and maternal mortality was reported globally. Under-five mortality fell from 13.0 million to 4.8 million (1) while maternal mortality dropped from 443,000 deaths (328 per 100,000 live births) in 2000 to 260,000 deaths (197 per 100,000 live births) in 2023 (2). These improvements were driven by increased investments in reproductive, maternal, newborn, and child health and nutrition (RMNCH), the scale-up of evidence-based interventions, and improvements in broader socio-economic determinants (3–5). Yet, despite significant gains, current approaches remain insufficient to address effectively the growing burden of maternal health and well-being throughout the life course (6, 7).

Community health workers (CHW) system can fill the gap between the high accessibility of antenatal care services and poor maternal and child health outcomes in the region, through a translation of health services and guidance on healthy behaviors within a cultural context. Complied evidence supports that CHW has been effective in frontline primary health care management in improving mother and child health. A meta-analysis of RCTs in Bangladesh, India, Nepal, and Malawi reported a 23% reduction in neonatal mortality and a 37% reduction in maternal mortality among women’s groups with participatory learning and action (8).

In the Philippines, maternal mortality has reduced notably by 35% from 127 to 84 deaths per 100,000 live births over the past two decades (2). The fertility rate also marked a decline during the same period, from 3.7 births in 2000 to 1.9 births per woman in 2023 (9). However, disparities in maternal and child health within the country persist, calling for holistic interventions to support marginalized populations (10, 11).

Eastern Visayas is a geographically isolated and disadvantaged area (12). According to the 2022 Demographic and Health Survey, the neonatal mortality rate was 13 deaths and under-five child mortality rate was 27 deaths per 1,000 live births in the Eastern Visayas (13). Moreover, the poverty rate in Eastern Visayas in 2018 was 49.5 percent, significantly higher than the national rate of 16.7 percent. In 2015 National Nutrition Survey (14), Eastern Visayas ranked in second place regarding malnutrition status, where 41.7% of children under 5 years were stunted, 8.4% wasted, and 29.5% underweight.

Barangay health workers (BHWs) serve as front-line workers, particularly critical roles in rural areas (15). BHWs deliver and support services related to maternal and child health, integrated community case management, HIV/AIDS, malaria, and tuberculosis control and implement national nutrition programs throughout the continuum of care. However, the impact of BHW programs on health outcomes is limited, likely due to limited training, resources, and a lack of community support (16).

### Intervention

1.1

#### Maternal, newborn, and child health (MNCH) project

1.1.1

The maternal, newborn, and child health (MNCH) project (2021–2025) was adopted as part of KOICA’s strategic partnership program, which attempted to harness the expertise and grassroots networks of Non-Governmental Organizations over 15 years. The MNCH project targets vulnerable households including Geographically Isolated and Disadvantaged Area (GIDA) in the provinces of West Samar, Northern Samar, East Samar, and Leyte provinces (Figure 1). Through active community engagement and decision-making involvement, the MNCH project aims to enhance access to and utilization of health services in these areas. To ensure the delivery of quality MNCH services at both facility and household levels, World Vision equipped health professionals and barangay health workers. Simultaneously, it has enhanced the availability and readiness of health facilities by reinforcing the referral system and providing essential equipment, medicines, and consumables.

**Figure 1 fig1:**
[figure not shown]
Timeline of household visits by barangay health workers from a timed and targeted care for families (ttCF) program (adopted from World Vision Korea).

### Timed and targeted care for family (ttCF)

1.2

The timed and targeted care for family (hereafter, ttCF) approach, a key MNCH component, adapts the Timed and Targeted Counselling (ttC) model by incorporating local contextual factors and emphasizing family participation and gender equality to improve maternal and child health during the first 1,000 days. The ttC is World Vision’s (WV) flagship program for maternal and child health emphasizing a family-inclusive and gender-transformative approach through the assistance of trained community-based health workers (CHWs) (17). ttC programs have been conducted in 38 different countries around the world (18). ttC programs have demonstrated a wider range of outcomes across the continuum of care including improved antenatal care and newborn health care, increased facility delivery, greater family planning uptake, enhanced breastfeeding and complementary feeding behaviors, hygiene practices, and child nutritional status (19–22). As ttC visits are conducted by community health workers or volunteers, the program strengthens access to primary health care and reinforces the community health system (23). According to the WHO Macroeconomics in Health Commission, an intervention is considered cost-effective if the cost per discounted life-year saved is below the national GDP per capita. Based on this criterion, ttC programs have been shown to be cost-effective (31). A ttCF monitoring tool was created through a collaborative effort across different sector experts from World Vision. The two key components of monitoring system are household registration and the development of a centralized database. For the register, a nine-page booklet was initially developed by World Vision International in 2015 and later modified by a partnership of the MNCH project team and the Department of Health (DOH)-Philippines for the contextualization of the tool. After extensive consultation with various stakeholders, the materials were printed in the second quarter of 2023.

The ttCF in the Philippines introduces several key adaptations compared to the previous ttC model. Not only barangay health workers (BHW) but also Barangay Nutrition Scholars (BNS) are also engaged in home visit counseling, expanding the reach of community-based health services. The Department of Health has also begun implementing the minimum requirement of eight antenatal care (ANC) visits, in line with WHO guidelines. This recommendation is incorporated into the CHW’s messaging, aiming to promote healthier pregnancies through the prevention, early detection, aiming to promote healthier pregnancies through the prevention, early detection, and referral of complications, while also encouraging enrollment in Phil health, the national health insurance program, to ensure financial access to these essential services. Under current DoH guidelines, a postnatal visit is defined as occurring within 45 days after delivery, extending the previous standard of 42 days to allow better follow-up and support. Furthermore, Shaken Baby Syndrome is indicated as a form of child abuse, highlighting the need for caregiver education and early prevention. The ttCF manual assigns specific roles to male caregivers and partners, which were not included in the previous ttC program.

The ttCF program trained BHWs and BNSs, supervised by the Rural Health Unit (RHU), to strengthen the capacity to support families in understanding the key maternal health practices from pregnancy to 2 years of life. In 2022, a total of 42 healthcare professionals (comprising doctors, nurses, and midwives) from 16 municipalities and three provincial health officers were trained with the ttCF training of facilitators (ToF) curriculum. In April–June 2023, these previously trained health workers trained 1,865 BHWs (female: 1,826; male: 39) for ttCF messages and counseling skills in their respective areas. Pregnant women and postpartum mothers with children 0–23 months of age have been visited by trained barangay health workers (BHWs) since July 2023. BHWs were provided with non-monetary compensation for household visits.

The ttCF database serves as the primary monitoring tool of the project by enabling a robust analysis of the collected data. As of December 2024, the database contains 6,280 ttCF households with pregnant and lactating women with infants 0–2 years old. The register is presented by BHWs during household visits, and the data is subsequently reported to RHU supervisors (e.g., rural health manager or nurses) then to each field facilitator to ensure minimal error prior to handing over the encoder. If there is missing data, the encoder returns the register to the field facilitators. If a common data issue is found in the registers, the field facilitator or program officer advises the BHWs to revisit the households and collect missing data. M&E officers validate the data and share the summary data with the research team.

## Methods

2

### Study purpose

2.1

The present study aims to describe the impact and implementation process of ttCF program on maternal and child health and nutrition outcomes and service utilization. To understand the impact and process of ttCF program in Eastern Visayas, Philippines, a comprehensive evaluation was planned with the following objectives: (1) to examine the impact of ttCF on utilization of maternal and child health services and continued maternal and child health and nutrition outcomes and (2) to conduct a process evaluation of the ttCF program using the RE-AIM evaluation framework: (1) reach; (2) impact/outcomes; (3) adoption; (4) implementation; and (5) sustainability. The evaluation framework is described in Figure 2. The research team, MNCH staff, and community health workers collaborate to establish the M&E system and collect various data.

**Figure 2 fig2:**
[figure not shown]
Monitoring and evaluation framework of a timed and targeted care for families (ttCF) program.

### Impact evaluation

2.2

#### Study areas

2.2.1

The study applies a quasi-experimental design in 12 municipalities, following pregnant women or mothers aged 15–49 years old with at least one child aged 0 to 11.9 months. Selection of 12 study municipalities was made through discussions with research team, MNCH team, and local governments. Out of the four MNCH project provinces, only West Samar and East Samar were included in the study due to their larger expected population size. Northern Samar province was excluded too far from the MNCH office in Tacloban where research management is made and are residing within West and East Samar provinces of Eastern Visayas. Out of 12 study municipalities, 6 municipalities of Taft, General MacArthur, Quinapondan from East Samar and Marabut, Basey, and San Jorge from West Samar were assigned intervention areas and the remaining 6 municipalities of Giporlos, Oras, and San Julian from East Samar and Pinabacdao, Hinabangan, and San Sebastian from West Samar were assigned as comparison areas.

#### Intervention

2.2.2

For the participants in the intervention group, 12 home visits are scheduled according to the manual, with 4 visits during pregnancy, 4 visits from birth to 6 months of child age, and 4 visits between 6 to 24 months of age. Twelve home visits are scheduled in total: during pregnancy (4 visits), from birth to 6 months of age (4 visits), and thereafter to 24 months after birth (4 visits) (Figure 3). The messages include a wide range of health and nutrition topics related to pregnancy, delivery, postnatal care, and early childhood childcare. These include tracking of pregnant women and children, WASH, breastfeeding, identification of danger signs, and referral (Supplementary Table 1). Health messages and counseling are delivered through storytelling techniques supported by visual materials. Through the use of visual materials and sharing of cases in the form of stories, questions are asked to discuss together what positive behaviors mothers and guardians are currently engaging in and what needs improvement. BHWs document the health practices observed and done by each household. For health practices not done by the household, negotiated agreements are established and recorded. In comparison areas, the government’s routine antenatal and postnatal health services are provided. Household visits by BHWs are practiced but not promoted by the government.

**Figure 3 fig3:**
[figure not shown]
Study areas (adopted from World Vision Korea).

Prior to the study enrollment, the research team obtained the lists of eligible pregnant women or postpartum women from BHWs, RHUs, and the MNCH project team. Pregnant or postpartum mothers with children aged 0–11.9 months are eligible for enrolment. Enumerators will assess eligibility and obtain informed consent through household visits. If two or more women in a household meet the eligibility criteria, the enumerator will randomly choose one. If there are multiple children within a household, the youngest child will be selected for the study.

#### Outcomes

2.2.4

Maternal-level outcome variables include antenatal care, facility-based delivery, and postnatal visits, including (1) 8 or more antennal visits (a new recommendation by the Philippine government), (2) dietary diversity, (3) timely postnatal care, (4) nutritional status (e.g., BMI), and (5) mental health. At the child level, outcome variables of focus will include (1) exclusive breastfeeding and continued breastfeeding, (2) minimum dietary diversity, and (3) prevalence of stunting (LAZ < -2). Background information on the individual (e.g., literacy, age, pregnancy status); household characteristics (e.g., size, residence location); prenatal, childbirth and postpartum care services; child nutrition and health status; and home visit counseling service will also be collected so that these can be controlled for or used for disaggregation in data analysis.

### Cross-sectional surveys

2.3

Multiple cross-sectional surveys have been conducted in 16 MNCH municipalities of all four provinces. The cross-sectional data will track the changes in health outcomes at the population level over the MNCH project period (2022, 2024, and 2025). Lot Quality Assurance Sampling (LQAS) was used to determine the sample size of the cross-sectional surveys. LQAS is used to assess a program by analyzing data produced by a small sample. LQAS recommends using 19 supervision areas (SA) as the primary data collection unit. In this survey, 19 barangays were randomly selected in each province. Barangays were selected using the Probability Proportional to Size (PPS) sampling method. The sample size of *n* = 19 and decision rule of *d* = 13 was selected to maintain *α* error of ≤10%, and *β* error of ≤10%. It is interpreted that 80% coverage is achieved when more than 13 positive responses out of 19 responses are recorded. In practice, on average, 10 households were surveyed per barangay, based on field feasibility. Starting from the first household, the enumerator moved in a predetermined direction, visiting households until eligible respondents from each target group were found. In barangays with fewer than 10 eligible households, enumerators surveyed adjacent barangays after consultation with a survey supervisor. In each province, the number of households assessed was 190. The midline and the endline surveys will assess trends of antenatal, delivery, and postnatal care from baseline, midline to endline. The same barangays will be revisited for the midline and endline surveys, with an adjusted sample size to enable trend analysis over time. Assuming that the proportion of 8 or more antenatal checkups (a recent recommendation by the Philippines government) at the baseline was 15.6%, we expect a total increase of 8% in the outcome for 4 years, a 2% annual increase from the baseline to the endline with significance level 5%, design effect of 2, and non-response rate of 10%. The minimum required sample size is 900 participants. Thus, 225 participants are included in each of the four provinces, and 56 participants in each of the 16 municipalities. Each Barangay is divided into segments containing a roughly equal number of households; a segment is then chosen at random. This process is repeated until approximately 11 to 12 eligible households are identified in each barangay.

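### The LQAS rule as worded (more than 13 of 19) fails an area truly at 80% coverage 16.3% of the time, above the stated 10% limit; 13 or more gives 6.8%

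*Protocol article*

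**What the plan says.** All the relevant design text is in section 2.3, Cross-sectional surveys, of the protocol article. LQAS is presented there as the basis for the survey sample size.

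- Design values: "The sample size of *n* = 19 and decision rule of *d* = 13 was selected", with the purpose given as "to maintain *α* error of ≤10%, and *β* error of ≤10" per cent.
- Operating rule, in the next sentence: "It is interpreted that 80% coverage is achieved when more than 13 positive responses out of 19 responses are recorded".
- Sample actually taken: "In this survey, 19 barangays were randomly selected in each province"; "In practice, on average, 10 households were surveyed per barangay, based on field feasibility"; "In each province, the number of households assessed was 190".

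The section gives no lower coverage threshold and does not say which error is alpha. It does not relate the rule for 19 responses to the 190 households. Section 3.2, Cross-sectional survey, describes the analysis as means and percentages, stratified and compared by province. It mentions no LQAS classification.

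**The concern.** An LQAS plan is defined by its sample size, its cut-off and the two error risks that follow from them. The article states all of these, and they do not agree. Counting 13 positives as a fail instead of a pass moves a substantial probability from one error to the other. A reader who applies the sentence literally would reject areas at the target coverage more often than the article says.

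A second, smaller question concerns scope. The stated error limits belong to a lot of 19 responses, whereas the survey collected about ten times that number per province, grouped within barangays. Without a sentence linking the two, the limits of 10% could be taken to describe the survey as carried out.

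**Working it through.** **Inputs from section 2.3:** n = 19; d = 13; both errors at most 10%; coverage level 80%; pass if more than 13 positives, so X ≥ 14.

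**Assumptions:** the 19 responses are independent, so X follows Binomial(19, p). The lower threshold is not given, so it is varied.

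**Formulas:** for a rule that passes when X ≥ c,

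- false-fail risk at true coverage p = P(X ≤ c − 1 | p) = Σ over k = 0 to c − 1 of C(19, k) p^k (1 − p)^(19 − k);
- false-pass risk at lower threshold p = P(X ≥ c | p).

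**Step 1: the stated limits against the rule as worded.** With c = 14, P(X ≤ 13 | 0.80) = 0.1631, or 16.3%. The stated limit of 10% is not reproduced. This result needs no lower threshold. Under this rule, true coverage must reach about 82.5% before the false-fail risk falls to 10%. Treating 80% as a level to be exceeded does not rescue the limits either, because the rule passes an area at exactly 80% with probability 1 − 0.1631 = 83.7%.

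**Step 2: one count lower.** With c = 13, P(X ≤ 12 | 0.80) = 0.0676, or 6.8%, which is within the limit. The difference, 0.1631 − 0.0676 = 0.0955, is the probability of exactly 13 positives.

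**Step 3: the other error, over assumed lower thresholds.**

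| Assumed lower threshold | False pass, 13 or more | False pass, 14 or more |
|---|---|---|
| 40% | 1.2% | 0.3% |
| 45% | 3.4% | 1.1% |
| 50% | 8.4% | 3.2% |
| 55% | 17.3% | 7.8% |
| 60% | 30.8% | 16.3% |

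With 13 or more, the false-pass risk stays at or below 10% for lower thresholds up to about 51%.

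**Step 4: is 13 the cut-off that the stated limits point to?** At 80% against an assumed 50%:

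| Pass rule | False fail at 80% | False pass at 50% |
|---|---|---|
| 12 or more | 2.3% | 18.0% |
| 13 or more | 6.8% | 8.4% |
| 14 or more | 16.3% | 3.2% |

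Only 13 or more keeps both at or below 10%. The false-fail limit on its own does not single out 13, since 12 or more also meets it.

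**Step 5: sensitivity to independence.** If the 19 responses were correlated (beta-binomial, assumed intracluster correlation 0.02 to 0.10), the false-fail risk at 80% would be 19.5% to 25.2% for 14 or more and 10.1% to 17.6% for 13 or more. The article does not say how 19 responses would be drawn, for example one per barangay, so this is a range and not an estimate.

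**Step 6: scope.** 19 barangays × 10 households = 190 per province. The article gives no cut-off or error rate for 190.

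**The case against.** The strongest reply is that nothing in the evaluation depends on the choice between 13 and 14. LQAS is described as the basis of the sample size. Sections 2.4.2 and 3.2 plan percentages or numbers by area, not pass/fail results. The quasi-experimental comparison does not use LQAS. The midline and endline surveys, with 225 participants per province, have their own calculation based on antenatal visits, with a design effect of 2. This reply stands, and it limits the severity. It does not remove the inconsistency, because the article states the cut-off and the error limits itself and they conflict.

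A reader might infer that the 13-of-19 rule was applied to the 190 clustered households, or that areas with adequate coverage have been declared failures. The documents support neither. No section applies the rule to the 190 households or to a barangay of about 10, and no classification is reported. What can be said is that the link between the rule and the sample is left unexplained.

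It is also fair to object that 13 or more has not been shown to meet both limits. That depends on a lower threshold of about 51% or less, which the article does not state.

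**Conclusion.** The rule as worded does not have the property claimed for it: the false-fail risk at 80% coverage is 16.3% against a stated maximum of 10%. This follows from the article's own figures and the usual independence assumption, and it holds whichever error is labelled alpha. The values n = 19 and d = 13 are workable. The fault is one count in the sentence that interprets them, and 13 or more brings the risk to 6.8%. Compliance with the second limit is conditional on the unstated lower threshold.

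On scope, the supportable conclusion is narrow: the error rates for 19 responses do not describe 190 households in 19 barangays, and the text should say where the rule applies. Severity is minor to moderate.

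**What to change.** 1. In section 2.3, change the operating rule to 13 or more positive responses out of 19.
2. State the lower coverage threshold and which error is alpha. If the threshold is above about 51%, 13 or more does not keep the false-pass risk within 10%, and the stated limit has to be revised.
3. Add one sentence saying whether the rule is used, for which unit, and how the 19 responses are drawn. State that its error rates do not refer to the 190 households per province.
4. If any 19-response classification was made with 14 or more, check the lots with exactly 13 positives. Only those change.

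The cost is two or three sentences of text, plus the check in item 4 if such classifications exist. No new data are needed, and the planned percentages by province are unaffected.

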Process evaluation study using the RE-AIM framework allows the utilization of various data sources produced during the MNCH program implementation (27). Our process evaluation attempts to reveal the program impact pathways and factors that may explain the impact of the ttCF program on maternal and child health outcomes. Multiple data sources will be used to assess the process evaluation components including a quasi-experimental study, multiple cross-sectional surveys, monitoring and performance records, and qualitative data collection. World Vision Philippines/World Vision Korea will prepare annual and semi-annual performance reports for internal review and grant reporting. Those reports will be used to extract the relevant data by the research team. World Vision’s Excel-based ttCF monitoring form has been used in several countries globally. Table 1 describes the key outcomes for each construct of the RE-AIM framework.

**Table 1 tab1:** The overview of RE-AIM framework components to conduct timed and targeted care for families (ttCF) process evaluation.

Components	Example of evaluation questions	Eligibility	Methodology
Reach (Percent of participants among the eligible population)	Percentage of pregnant women enrolled in ttCF program among eligible mothers	Pregnant women or women with one or more children aged 0–23 months in 16 project municipalities	ttCF Monitoring records World Vision’s performance Report Records from Rural Health Unit (RHU)
Impact (Impact/effectiveness at the individual level)	Percentage of access to postpartum care services Percentage of Exclusive breastfeeding Percentage of Minimum dietary diversity among children 6–23 months of age	Pregnant women and mothers of children aged 0–23 months in 16 project municipalities	Secondary data of baseline survey (2022) Midline (2024) and Endline (2025) Survey Cohort surveys (2023–2024)
Adoption (Application rate of Project activities)	Percentage of BHW who actually performed ttCF home visits out of all community health workers in the project area	~2000 BHW in 16 project municipalities	ttCF Monitoring record World Vision’s performance Report Qualitative study (2024)
Implementation (The extent to which the project was actually executed compared to planning)	Number of households where BHW conducted home visit counseling Number of BHW who completed ttCF training	~2000 BHW in 16 project municipalities	World Vision’s Performance Report ttCF Monitoring records

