### Cross-sectional survey

3.2

A total of 720 households across four provinces were included in the baseline survey. The baseline data collection was conducted in July 2022 in East Samar/Leyte and in October 2022 in Northern/West Samar. The midline study was conducted in September 2024 (Table 1) and the endline study is scheduled for September 2025.

Exploratory data analysis will be conducted to calculate mean (SD) and percentages for all variables collected during different surveys. Descriptive statistics will be stratified by province (East Samar, West Samar, Leyte, and North Samar) and comparability across the four provinces will be tested using *χ*^2^ tests for categorical variables and Student’s *t*-tests for continuous variables. Key indicators will be selected to assess health service utilization during ANC, delivery, and PNC, family planning, and maternal and child nutritional status. These will include the proportion of women attending at least four ANC visits, receiving skilled birth attendance, obtaining postnatal care within 48 h of delivery, using contraceptives, and the prevalence of undernutrition among mothers and children under 5 years.

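### Trends in antenatal, delivery and postnatal care are read by survey round, but the midline birth window straddles the July 2023 launch, so a constant effect would look like a midline-to-endline rise of 3 to 4 points

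*Protocol article*

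**What the plan says.** Five statements in the protocol article bear on this point.

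- Purpose (section 2.3): "The midline and the endline surveys will assess trends of antenatal, delivery, and postnatal care from baseline, midline to endline".
- Sampling areas (section 2.3): "The same barangays will be revisited for the midline and endline surveys, with an adjusted sample size to enable trend analysis over time".
- Eligible population (Table 1, Impact row, which lists the 2022, 2024 and 2025 surveys among its sources): "Pregnant women and mothers of children aged 0–23 months in 16 project municipalities".
- Dates (section 3.2): "The baseline data collection was conducted in July 2022 in East Samar/Leyte and in October 2022 in Northern/West Samar". For the later rounds: "The midline study was conducted in September 2024 (Table 1) and the endline study is scheduled for September 2025".
- Start of the intervention (section 1.2): pregnant women and mothers "have been visited by trained barangay health workers (BHWs) since July 2023".

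Section 2.3 sizes the survey for a rise of 8 points in the proportion with eight or more antenatal checkups, from 15.6%, at 2 points per year. The article gives no restriction by delivery date for the birth-related indicators.

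**The concern.** The number of antenatal visits, the place of delivery and the timing of postnatal care are settled around one birth and do not change afterwards. A survey that takes mothers of children up to 23 months old averages these events over the preceding two years, so the survey date is a poor label for when they happened.

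Two separate things follow when the rounds are 12 months apart and the programme starts inside the first look-back period.

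1. The mix of births before and after launch changes between midline and endline. A programme that works equally well throughout would seem to improve.
2. The two look-back periods share births. A genuine change among births after midline is averaged with births that midline already covered.

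The Discussion says that mid-term impact data will inform decisions on planning, funding and sustainability. A midline that understates the effect, followed by a step that overstates recent progress, could mislead those readers.

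**Working it through.** **Inputs from the article.** Midline September 2024; endline September 2025; look-back 24 months (Table 1); home visits from July 2023; assumed rise 8 points in total, 2 points per year.

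**Assumptions.** Births spread evenly over each window; surveys in mid-September, varied over the month; pregnancy of 9 months; launch on 1 July 2023; a constant 8-point effect, borrowed from the plan's total increase.

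**The plan's own figure.** Comparing 15.6% with 23.6% at two-sided 5%, with 80% power (assumed, as power is not stated for this calculation) and a continuity correction, needs 410 per survey. Then 410 × 2 = 820, and 820 / 0.90 = 912, close to the stated 900. The point below does not affect this figure.

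**Windows.** Midline births run from mid-September 2022 to mid-September 2024; endline births from mid-September 2023 to mid-September 2025. Midline falls 14.5 months after launch. The endline window opens 2.5 months after launch.

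**Exposed share of births.**

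| | Midline | Endline |
|---|---|---|
| Born after launch | 14.5/24 = 60% | 24/24 = 100% |
| Whole pregnancy after launch (born from April 2024) | 5.5/24 = 23% | 17.5/24 = 73% |
| Mean share of pregnancy after launch | (9 × 0.5 + 5.5)/24 = 42% | (6.5 × 0.639 + 17.5)/24 = 90% |

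Here 0.639 is the mean exposed share for births between 2.5 and 9 months after launch: (2.5/9 + 1)/2. Moving the survey date within September gives 58–62% for the first midline cell. The second row becomes 21–25% and 71–75%, and the third 40–44% and 89–92%.

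**What a constant 8-point effect would look like.**

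- Delivery and postnatal care: 8 × 0.604 = 4.8, then 8.0; rise 3.2.
- Antenatal care, effect proportional to exposed pregnancy: 8 × 0.417 = 3.3, then 8 × 0.902 = 7.2; rise 3.9.
- Antenatal care, effect only with full exposure: 8 × 0.229 = 1.8, then 8 × 0.729 = 5.8; rise 4.0.

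With a constant effect of 6 points the three rises are 2.4, 2.9 and 3.0. With 10 points they are 4.0, 4.9 and 5.0. All exceed 2 points.

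**Dilution.** The shared period is 12 of 24 months, or 50% of each window. A change of D points confined to births after midline adds 0 at midline and D × 12/24 = D/2 at endline.

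**Other look-back lengths.** With 60 months, the share born after launch goes from 24% to 44%, a rise of 8 × 0.20 = 1.6 points, and the windows share 80%. With 12 months, the windows do not overlap and the delivery and postnatal rise is nil. Fully exposed pregnancies still go from 5.5/12 = 46% to 100%, so 3.7 becomes 8.0, a rise of 4.3.

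**The case against.** The strongest reply is that the 24-month window is inferred. Section 2.3 speaks only of eligible respondents in each target group. The 0–23 months stands in a Table 1 row that also covers the cohort, which enrolled mothers of children aged 0–11.9 months, and section 3.2 mentions undernutrition in children under 5 years. This stands as a limit on the exact figures. Still, Table 1 is the only eligibility the article states for these rounds, and an exposure shift remains at 60 months and, for antenatal care, at 12 months.

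Second, the contrast that the plan sizes is baseline to endline. That is correct. Baseline births precede the launch and endline births follow it, so a reader who infers that the whole trend is spurious goes too far. At most, the antenatal effect at endline is somewhat diluted by pregnancies already under way at launch.

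Third, if more births in the window were exposed, coverage in that window truly rose, and the plan aims to track population-level change. This also stands, and it is why the round-based figures can be kept. They fail only as a measure of progress between the two survey dates.

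Fourth, section 2.4.4 has survey respondents asked how many counselling visits they had, and relates municipality-level dose to outcomes. That is useful, but it does not change the time axis of the trend.

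Two stronger readings are tempting. One is that the overlap itself manufactures the improvement. It does not; overlap only dilutes, and the rise comes from the midline window straddling the launch. The other is that the same women are counted twice. The article shows shared eligibility, not shared sampling: segments are chosen at random and about 11 to 12 households are taken per barangay.

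**Conclusion.** The point holds for the midline-to-endline step in antenatal, delivery and postnatal care. Under the Table 1 window and evenly spread births, a constant 8-point effect would appear as a rise of about 3 points (delivery and postnatal care) to 4 points (antenatal care), against an expected 2 points per year. A real change confined to births after midline would appear at about half size.

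The point does not reach the baseline-to-endline comparison, the sample size, or current-status child indicators such as breastfeeding, dietary diversity and growth. Pregnant respondents without a recent birth lie outside the argument. It is a weakness in how one step of the trend would be read, and it is cheap to repair.

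**What to change.** Keep the round-based figures. For antenatal, delivery and postnatal indicators, add a pooled analysis of the three rounds by the child's delivery date relative to launch, for example before July 2023, July 2023 to March 2024, and April 2024 onward. Cluster the errors by barangay, since the same barangays are revisited. Base any statement about progress between midline and endline on this analysis. State in section 2.3 the child-age window that applies to each round.

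The cost is a little more analysis and smaller numbers in each delivery period. The child's age is already needed to apply the eligibility criterion, and no new fieldwork is involved.

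Two alternatives are not recommended. Restricting each round to births in the preceding 12 months would about halve the births and, as shown above, would leave a 4.3-point artefact for antenatal care if full exposure is needed. Removing births that appear in both rounds would need respondents to be linked across surveys, which the article does not describe.
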